**Fig. 1 fig1:**
[figure not shown]
Study Design.

**Setting:** The study will be conducted at the Irish TRUST site. The hub centre for the Irish site was located at the Mercy University Hospital, Cork with five satellite sites located at Waterford University Hospital, Bantry General Hospital, Kerry General Hospital, St John's Hospital Limerick and Vista Primary Care Centre, Naas. A total of 115 participants were recruited from these Irish sites and randomised to the TRUST Trial.

**Population:** As this is a SWAT within the TRUST trial, the study sample is determined by the trial. This study will consist of all TRUST participants recruited in the Irish site (n = 115).

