#### Focus groups

2.1.1

Three semi-structured focus groups will be conducted with four to eight TRUST participants per focus group. Participants for this phase will be determined based on the geographical feasibility of carrying out the focus groups. Cork is the main site for TRUST in Ireland therefore all Cork-based patients (n = 38) will be contacted via letter and invited to participate in one of three focus groups in the Cork TRUST site. The sessions will be led by an independent qualitative researcher. A topic guide will be used to guide the focus groups. The Consensus-Oriented-Decision-Making (CODM) model will be used in order to guide the group to reach a consensus. The CODM model steps [8], [9] include:1Framing the topic2Open discussion3Identifying underlying concerns4Collaborative proposal building5Choosing a direction6Synthesizing a final proposal7Closure.

**Analysis:** Focus group recordings will be transcribed verbatim and entered into NVivo Version 11 for thematic analysis. Braun and Clarke [9] guidelines will be followed when thematic analysis is being performed. Identified themes will be used to model a patient-preferred method for the dissemination of results.

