#### Patient and public expert group

2.1.2

A patient and public expert group will be established to assess the content on and test the validity of the proposed trial result dissemination method. This group will consist of three to five TRUST participants recruited from the Cork site. A series of consultations will take place with this group in order to iteratively refine the format of the patient-preferred dissemination method.

**Outcome:** The findings from this phase will be used to identify and develop the patient-preferred end-of-trial result dissemination method.

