### Phase two: intervention

2.2

**Aim:** To disseminate the results of the TRUST Trial to TRUST participants.

**Design:** A prospective, randomised, single-blind, parallel-group intervention group trial.

**Method:** Results will be disseminated to participants in Ireland after the final results of the trial are published in April 2017. Simple random allocation will be used to randomise participants to the intervention or comparison group. Participants from the patient and public expert group (n = 3) will not be randomised as they will have already reviewed the content of the intervention method prior to randomisation. The intervention group will receive the PPI informed dissemination method and the comparison group will receive the standard dissemination method developed by the lead study site in Glasgow, Scotland. Participants will be blinded to the result method they will receive. One member of the research team will be un-blinded in order to perform the randomisation and distribute the results of the trial.

**Outcome:** All TRUST participants will receive the results of the TRUST Thyroid Trial.

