### Phase three: quantitative data collection

2.3

**Aim:** To measure the impact of PPI on patient understanding of end-of-trial results.

**Design:** Quantitative questionnaire evaluation of the intervention.

**Method**: A questionnaire will be developed and validated to measure patient understanding of the end-of trial results. The questionnaire will be developed in consultation with experts in the area of subclinical hypothyroidism and scale development. It is expected that the questionnaire will contain no more than 10 items which will be measured on a LIKERT scale. While there is debate in the literature regarding the minimum required sample size for exploratory factor analysis, it has been established that a ratio of 10 participants per variable is appropriate to produce solutions that are accurate representations of the population parameters [10]. Questionnaire items will be developed by adapting existing questionnaires and new items will be generated where necessary through consultation with the content and scale development experts and the patient and public expert group. Prior to administering the full questionnaire, it will be reviewed by the patient and public expert group to assess content and face validity. Any suggestions and changes made by this group will be incorporated into the final questionnaire. The questionnaire will be sent to the intervention and comparison groups one week after they have received the results of the trial.

**Analysis:** Completed questionnaires will be entered into SPSS software. The psychometric properties and construct validity of the questionnaire will be examined with exploratory factor analysis, using principal component analysis (PCA). PCA is a useful exploratory factor analytic tool that can be incorporated into the development and refinement of new scales [11]. In this case, PCA will allow for the maximum amount of variance in patient understanding to be explained by the smallest number of constructs. Internal consistency of the questionnaire will be investigated using Cronbach's alpha coefficient. Where possible, participant responses will be analysed using descriptive and inferential (Chi-square test) statistics. The researcher carrying out the input and analysis of this data will be blinded to the participants' allocation status. Subgroup analysis will also be conducted to measure how patient understanding is impacted by age, gender, education status and study site attended.

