**Outcome:** The primary outcome will be difference in levels of patient understanding between the intervention and comparison groups. This will measure the impact of PPI on patient understanding of end of trial results.

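### The randomised comparison estimates the effect of one dissemination method against another; it cannot attribute the difference to PPI, as the phase three aim and outcome say it will

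*Protocol article*

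**What the plan says.** The aim of phase three (section 2.3) is "To measure the impact of PPI on patient understanding of end-of-trial results". The outcome paragraph of that phase first defines the quantity to be compared: "The primary outcome will be difference in levels of patient understanding between the intervention and comparison groups". It then interprets that quantity: "This will measure the impact of PPI on patient understanding of end of trial results".

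The groups are defined in section 2.2. One arm gets the product of phase one: "The intervention group will receive the PPI informed dissemination method". The other arm gets a method that comes from elsewhere, since the text says that "the comparison group will receive the standard dissemination method developed by the lead study site in Glasgow, Scotland". Individual participants are the unit of randomisation.

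The intervention is built in phase one. The Setting paragraph of the Methods says "The study will be conducted at the Irish TRUST site". The focus groups (section 2.1.1) are held with Cork participants, and "Identified themes will be used to model a patient-preferred method for the dissemination of results". An expert group, also drawn from Cork (section 2.1.2), then helps to "iteratively refine the format of the patient-preferred dissemination method".

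The Abstract and the last paragraph of the Background put the overall aim differently. There it is to find, build and evaluate a method that patients prefer for receiving the TRUST results. Measuring the effect of PPI is not part of that statement.

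**The concern.** Two sentences in section 2.3 give the comparison a meaning that the allocation in section 2.2 cannot support. A difference between the arms would show that recipients of one method understood the results better than recipients of the other. It would not show that involving patients in development was the reason, because the two methods also come from different sites and teams.

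This matters because the Background presents measurement of PPI's impact as an unmet need and notes that earlier work struggled to isolate what patient involvement contributes. A reader of the eventual report would naturally take a positive result as filling that gap. A null or negative result could equally be misread as evidence that PPI does not help, when it might reflect a strong Glasgow product.

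**Working it through.** No arithmetic applies. The article gives no figure for this claim, and the question is what the contrast can identify. The passages can be set side by side.

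**1. What each arm contains**

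| | Intervention arm | Comparison arm |
|---|---|---|
| Number of methods | One | One |
| Developed by | Irish site, with Cork focus groups and a Cork expert group (2.1.1, 2.1.2) | Lead site in Glasgow (2.2) |
| Patient input to development | Yes | Not stated |

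**2. What would be needed to isolate PPI.** Two factors are in play: PPI (with or without) and developing site and team (Irish or Glasgow). Isolating PPI needs at least two methods that differ in PPI and share the other factor. The Irish method with PPI exists. The Irish method without PPI does not. The Glasgow method exists, but its level of patient input is not given. No pair of arms holds site and team constant.

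**3. What the difference represents.** As a simple additive illustration, write D for the expected difference in understanding between the arms:

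D = (effect of PPI) + (effect of developing site and team, and of any product difference not caused by PPI)

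Randomising participants gives an unbiased comparison for D. That is one quantity with two unknown components. Any split between them fits the same D, including a split in which the PPI component is zero or of opposite sign.

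**4. Whether sample size helps.** It does not. More participants would estimate D more precisely. The number of methods per condition would still be one, so nothing in the data would separate the two components.

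**5. Whether the contrast is even PPI against no PPI.** The article calls the comparator the standard method and does not describe how it was made. If patients had some input in Glasgow, the contrast would be between more and less involvement, by an unknown amount.

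**6. Consistency within the article.** The first sentence of the outcome paragraph and the overall aim in the Abstract and Background describe a method-against-method comparison, which the design delivers. Only the phase three aim and the attribution sentence go further.

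**The case against.** The strongest reply is that PPI acts through the product. Sections 2.1.1 and 2.1.2 plan for patients' views to shape the method and its format. If the method is shorter or clearer because patients asked for that, crediting PPI is reasonable, and treating the feature as a confounder would be wrong. This stands. A reader might infer that every difference in medium, length, reading level or content confounds the comparison. The article does not support that: such differences are partly the intended route of action, and since neither product is described, their existence is not documented. What remains is narrower. A different team at a different site might well have produced a different product anyway, and separating that part from the PPI part needs a counterfactual method from the same team, which the plan lacks.

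A second reply is that the outcome is already defined correctly, as a difference between the two groups. That is also true, and it confines the fault to one interpretive sentence and one aim.

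Two other stronger readings should be resisted. One is that the trial comparison is invalid. It is not: participants are randomised, and the two methods can be compared as packages. The other is that the article offers its conclusion about PPI as a template for other trialists. In the Abstract and Discussion it is the protocol that is offered as a template. The evidence promised there concerns how best to disseminate results, and the design can contribute to that.

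**Conclusion.** The point holds in a limited form. The phase three aim and the attribution sentence claim a property that the design does not have. The randomised contrast identifies the effect on understanding of receiving this PPI-informed method rather than the Glasgow standard method. It does not identify the effect of PPI as a process, because PPI is completely aliased with developing site and team and with any product difference that PPI did not cause.

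No numerical size can be given for the error. It is a matter of identification, and the documents contain nothing from which the non-PPI component could be bounded.

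The conclusion rests on two readings of the article. First, the intervention is developed by the Irish team; this is inferred from the setting and from the Cork-based phase one work. Second, there is no further arm beyond the two in section 2.2. Randomisation, data collection and the planned comparison are unaffected.

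**What to change.** - Restate the phase three aim in section 2.3 as estimating the effect on patient understanding of receiving the PPI-informed method rather than the Glasgow standard method.
- Replace the attribution sentence in the outcome paragraph with the same statement. The sentence before it, which defines the primary outcome, can stay.
- Confine the conclusion to that comparison, in line with the overall aim in the Abstract and Background.
- State as a limitation that PPI cannot be separated from developing site and team, and that the extent of patient input to the Glasgow method is not given.

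The cost is a change of wording in a few places and a narrower claim: the study would no longer be presented as measuring the impact of PPI itself. Sample, allocation and analysis stay as they are. If attribution to PPI is essential, the design would need a comparator prepared by the same team from the same source material without PPI. That is a much larger change and is not needed for the overall aim.

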## Discussion

3

The importance of engaging patients in the design and conduct of clinical trials is increasingly recognised [1]. This protocol sets out a rigorous approach to engaging patients in decisions about how best to communicate trial results with trial participants. It will provide a useful template for other clinical trialists who wish to enhance patient and public involvement and additionally, will provide empirical evidence on how trialists should best disseminate study results to their participants.

## Ethics approval

The research was approved in Ireland by the Clinical Research Ethics Committee of the Cork Teaching Hospitals, UCC, Ref ECM 4 (t).

